### Web-based CBT intervention (CBT4CBT)

After completing the inpatient care (at discharge), the patients randomly assigned to the experimental condition will receive the TAU + CBT4CBT a web-based treatment which, as previously stated was tested on individuals with cocaine use disorder in America by the team of Carroll et al. (18). Depending on the patients' personal situation, they will have two options for receiving the treatment: they will be provided with access to the computer program in a small private room within the addictive behaviors outpatient unit or they will be provided with code access for being able to do it from home. In all instances, a psychologist will guide participants through their initial use of the CBT4CBT program and she will be available to answer questions and assist participants each time they use the program (the CBT4CBT and TAU treatments are always explained by a woman). The participants will access the program through an identification/password system to protect confidentiality.

The CBT4CBT program is intended to be user-friendly. The multimedia style of the program is based on elementary-level computer learning games, and the material is presented in a range of formats, including graphic illustrations, videotaped examples where a story with different characters with substance addictions display common risk situations and several ways to cope with them (highlighting the most functional one), verbal instructions, audio voiceovers, interactive assessments with a dichotomous response type, and practice exercises, such as decisional balances that participants must complete with their own arguments. The program consists of six skills (understanding and changing patterns of substance use, coping with craving, refusing offers of drugs, problem-solving skills, identifying and changing thoughts about drugs and improving decision making skills) organized in seven modules of 30 min duration based on a CBT manual published by the National Institute on Drug Abuse and it covers the following core concepts: (1) recognize the triggers, (2) stand up for yourself, (3) deal with craving, (4) stop and think, (5) plan don't panic, (6) go against the flow and (7) stay safe. Each participant has its own credentials to enter the platform, and once in the web-based treatment, the first module will also provide a brief explanation of how to use and navigate the program. Following completion of the first module, the participants can access the rest of the modules (see Table 1). Additional details regarding CBT4CBT can be found elsewhere (14, 19, 22).

**Table 1 T1:** Content of the 8-week CBT4CBT program.

**Session**	**Topics covered**
Module 1: Recognize the triggers	Identify, recognize and change triggers and patterns of use
Module 2: Stand up for yourself	Assertiveness and learning the ability to say “no” when someone is offering drugs
Module 3: Deal with craving	Strategies to manage substance related craving and urges
Module 4: Stop and think	Identify distorted beliefs about drugs, as well as challenging and changing negative thoughts that are maintaining the substance use
Module 5: Plan don't panic	Improve skills and strategies to facilitate decision-making without using drugs
Module 6: Go against the flow	Improve skills to manage adverse events other than using cocaine or other substances to face problems
Module 7: Stay safe	Develop skills to prevent relapse and maintain healthy behaviors

Researchers [name] and [name] monitor whether participants complete the modules of the CBT4CBT treatment and report it in a separate excel sheet. Also, the completion of the modules can be tracked entering to the section “providers” in the CBT4CBT website (http://www.cbt4cbt.com). Apart from whether the participant has completed or not the module, the researcher can check the percentage of completion of the module and the time spent on it.

## Data collection and assessment

### Assessment

There will be 6 time-point assessments: *TO-PRE:* within the inpatient unit, before starting psychological treatment but once the patients are stabilized from cocaine withdrawal; *T1-PRE:* after inpatient treatment before starting outpatient treatment (TAU or TAU + CBT4CBT); *T2-POST:* once the 8-w outpatient treatment is completed (TAU or TAU + CBT4CBT); *T3-FU: 1* month follow-up; *T4-FU:* 3 months follow-up; *T5-FU:* 6 months follow-up. Additionally, the presence of benzoylecgonine (metabolite of cocaine) in urine will be assessed weekly during the 8 w period of web-based treatment (see Table 2).

**Table 2 T2:** Schedule of enrolment, interventions and assessments.

**Indicator**	**Enrolment (inpatient treatment)**	**End of inpatient treatment**	**TAU + CBT4CBT/TAU (weekly control)**	**Post treatment (TAU + CBT4CBT/TAU)**	**Follow-up (1, 3, 6 m)**
Inclusion/exclusion criteria	XXXX				
Informed consent signature	XXXX				
Allocation	XXXX				
Sociodemographic data collection	XXXX				
**Data about web-based CBT4CBT intervention program**					
Program satisfaction (CSQ-8)		XXXX		XXXX	
Knowledge about program content	XXXX			XXXX	
System Usability Scale (SUS)				XXXX	
User Experience Questionnaire (UEQ)				XXXX	
Usefulness, Satisfaction and Ease of use (USE) questionnaire				XXXX	
**Hospitalization data- anthropometric and biochemical variables**					
Toxicology urinalyses screen	XXXX		XXXX	XXXX	XXXX
Height	XXXX				
Weight	XXXX	XXXX		XXXX	XXXX
Cardiac frequency	XXXX	XXXX		XXXX	
Used substances (previous 30 days)	XXXX	XXXX		XXXX	XXXX
Substance use history	XXXX				
**Psychopathological status, dependence and craving**					
Beck Depression Inventory (BDI)	XXXX^**^	XXXX		XXXX	
State-Trait Anxiety Inventory (STAI)	XXXX^**^	XXXX		XXXX	
Mini International Neuropsychiatric Interview (MINI)	XXXX^**^				
Cocaine Selective Severity Assessment (CSSA)	XXXX^**^	XXXX		XXXX	
Severity of Dependence Scale (SDS)	XXXX^**^	XXXX		XXXX	
Weiss Cocaine Craving Scale (WCS)	XXXX^**^	XXXX		XXXX	XXXX
Symptom Check List Revised (SCL-90-R)	XXXX^**^	XXXX		XXXX	XXXX
**Other addictive behaviors**					
South Oaks Gambling Screen (SOGS)	XXXX^**^			XXXX	
Yale Food Addiction Scale 2 (YFAS-2)	XXXX^**^			XXXX	
DSM-5 criteria for Internet Gaming Disorder (IGD)	XXXX^**^			XXXX	
Hypersexual Behavior Inventory (HBI)	XXXX^**^			XXXX	
**Emotional regulation and personality**					
Sensitivity to Punishment and Sensitivity to Reward Questionnaire (SPSRQ)	XXXX^**^				
Difficulties in Emotion regulation Scale (DERS)	XXXX^**^	XXXX		XXXX	
Emotion Regulation Questionnaire (ERQ)	XXXX^**^	XXXX		XXXX	
UPPS-P Impulsive Behavior Scale (UPPS-P)	XXXX^**^	XXXX		XXXX	
Multidimensional Assessment of Interoceptive Awareness (MAIA)	XXXX^**^				

** Once the patient is stabilized from cocaine withdrawal (up from 48 to 72 h after hospitalization).

### Instruments

Primary outcome measures will be treatment dropout (two consecutive failures to attend and not answering the phone) and relapse (cocaine use: number of positive urine specimens submitted, percent negative urine screens, percent days of abstinence, self-reported frequency of cocaine use). Treatment dropout will be determined throughout the attendance at the appointments with the clinician (TAU or TAU + CBT4CBT), which will be carried out weekly during the 8-week period of treatment and at follow-up points. Relapse will be determined according to the participants' reports and throughout the presence of benzoylecgonine (metabolite of cocaine) in urine assessed with the Kinetic Microparticle Interaction test in a Solution (Roche Diagnostic System, Inc., Sommerville, NJ).

Secondary measures will cover sociodemographic variables and anthropometric measures (weight and high), cocaine craving, psychopathological symptoms and comorbidities, other addictive behaviors, personality traits, emotion regulation skills and CBT4CBT usability as well as treatment satisfaction.

Psychopathological symptoms and comorbid disorders will be assessed with a Clinical interview based on the DSM-5 diagnostic criteria for addictive behaviors, the MINI international neuropsychiatric interview (23), the Symptom CheckList-90 items-Revised (SCL-90-R) (24, 25), The State-Trait Anxiety Inventory (STAI) (26, 27) and the Beck's Depression Inventory (BDI) (28, 29). Craving and compulsive drug use will be measured with the following self-reported questionnaires: Severity of Dependence Scale (SDS) (30, 31), Cocaine Selective Severity Assessment (CSSA) (32, 33), Weiss Craving Scale (WCS) (34, 35). Other addictive behaviors will be measured, including gambling with the South Oaks Gambling Screen (SOGS) (36, 37), food with the Yale Food Addiction Scale 2 (YFAS) (38, 39), gaming with the DSM-5 criteria for internet gaming disorder (IGD) (40, 41) and sexuality with the Hypersexual Behavior Inventory (HBI) (42, 43).

Different facets of emotion regulation will be assessed with the following self-reported questionnaires: Difficulties in Emotion Regulation Scale (DERS) (44, 45), Emotion regulation questionnaire (ERQ) (46, 47), and Multidimensional Assessment of Interoceptive Awareness (MAIA) (48, 49). Impulsive related traits will be measured with the UPPS-P Impulsive Behavior Scale (50, 51) and the Sensitivity to Punishment and Sensitivity to Reward Questionnaire (SPSRQ) (52). Finally, treatment satisfaction will be assessed through the Client Satisfaction Questionnaire (CSQ-8) (53, 54), usability of the intervention will be assessed using the System Usability Scale (SUS) (55, 56), user experience will be assessed by the User Experience Questionnaire (UEQ) (57, 58) and usefulness, satisfaction and ease of use will be assessed with the Usefulness, Satisfaction and Ease of Use (USE) questionnaire (59, 60).

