### Aims of the study

The aim of the present study is to evaluate whether adding a web-based cognitive behavioral therapy (CBT4CBT) to standard cocaine use disorder treatment improves treatment outcomes in a Spanish sample of patients with severe CUD (that require inpatient treatment). To do so, two primary outcomes are considered: (1) treatment retention (vs. dropout) and, (2) relapse (number of positive urine specimens submitted, percent negative urine screens, percent days of abstinence, self-reported frequency of cocaine use). As secondary outcomes the following variables are measured: craving, psychopathological symptoms, days of any drug use, CBT4CBT usability and treatment satisfaction.

The secondary objectives of the study are two-fold: (a) To explore differences between men and women in treatment response; (b) To explore if comorbid psychopathological symptoms, other addictive behaviors, craving and emotion regulation difficulties are predictive factors of treatment outcome at the end of inpatient treatment as well as at the end of the 8-week CBT4CBT + TAU or TAU and at follow-ups (1, 3, and 6 month).

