### Design and settings

This is an unicentric national open-label-randomized clinical trial focused on the improvement of cocaine use disorder treatment as usual (TAU) outcomes through the implementation of a web-based CBT treatment (CBT4CBT). The study was approved by the Research Ethics Committee of the Hospital de la Santa Creu i Sant Pau, project number IIBSP-CBT4CBT-2020-1116.

The present RCT has two arms: arm A (TAU) and arm B (TAU + CBT4CBT). All individuals with cocaine use disorder coming to our inpatient unit for cocaine detoxification will receive treatment as usual (TAU), which will consist of a multidisciplinary approach including psychiatrists, psychologists and nurses. The hospitalization for detoxification begins with the removal of all drugs and, during hospitalization, psychiatrists adjust medication in accordance to cocaine withdrawal symptoms. Additionally, individuals also receive daily psychological interventions based on motivation for change, craving management, assertive communication, problem solving skills and relapse prevention. Nursing staff carries out necessary therapeutic actions, such as taking vital signs, administering medications, provide space for emotional venting and conducting group therapies addressing motivation for change. After a mean of 14 days from admission, inpatients are discharged and placed to either TAU (day care treatment as usual + weekly outpatient follow up) or TAU + CBT4CBT (day care treatment as usual + weekly outpatient follow up and CBT4CBT). The intervention will be discontinued in case of request by the participant. Finally, to ensure adherence to intervention, after one unjustified absence rated by the psychologist, a phone call will be done (see Figure 1).

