**Figure 1 F1:**
[figure not shown]
Study design.

Within the framework of the study and with the purpose of introducing the subsequent outpatient treatment, all patients in our inpatient unit for cocaine detoxification who are part of the study will also receive individual psychological CBT based treatment with motivational strategies, emotional regulation skills for mood symptoms and craving management, as explained previously. After completing the inpatient care (at discharge of inpatient care), patients will be randomly assigned to the CBT4CBT + TAU or to TAU. The randomization will be centralized through Clinapsis (http://www.clinapsis-estudis.com/) and all data will be handled through this same platform. Clinapsis is a friendly-user platform where all data from participants is stored. To ensure the transparency and the achievement of ethics procedures, the Central Clinical Research and Clinical Trials Unit of Research Institute of the Hospital de Sant Pau can access the platform to monitor the data collection and management. In addition, the two researchers who provide the psychological strategies during both the inpatient and outpatient treatment phase and carry out the assessments ([name] and [name]) also have access to Clinapsis to check whether all data is completed and, subsequently, export it to the software Statistical Package for Social Sciences (SPSS) v. 26.0. Once the database is crated in SPSS, authors will manage the database removing duplicates, identifying missing values and setting up all the variables in order to conduct the statistical analyses in SPSS. Any imbalance in the number of participants in each treatment arm due to non-adherence to treatment protocol prior to starting CBT4CBT but after arm allocation, will also be centralized through Clinapsis.

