## Discussion

CBT4CBT is a CBT web-based treatment which concomitant to TAU has shown to improve current treatments in multiple US-based studies (18–20). However, up to date it has never been implemented in Spain.

This study aims to improve current evidence-based treatments for severe CUD (that requires inpatient treatment) through the implementation of a more intensive and extensive treatment which is grounded on a web-based CBT approach (CBT4CBT). Additionally, predictive factors for treatment outcome will be assessed. The main strength and contribution of this study will be the enhancement of CUD treatment, using a concomitant web-based treatment approach to TAU. CBT4CBT has the potential to optimize current treatments by facilitating daily access to it when needed. This study also explores different secondary measures (i.e., sociodemographic, cocaine use related variables, craving, personality traits, as well as comorbid psychopathology and other addictive behaviors) that can help to better understand predictive factors of treatment outcomes at two different clinical settings (i.e., inpatients treatment and day care treatment + CBT4CBT) and at 6 different time points (end of each treatment setting and at three different follow-up points−1, 3, and 6 months after treatment-). This can lead to the possibility of targeting specific characteristics in a population of severe CUD and to individualize treatments accordingly for aiming to a better outcome. Furthermore, this study will take into account a gender perspective and explore gender differences in predictive factors for treatment outcome and the efficacy of CBT4CBT.

The potential limitations of this study are the exclusion of patients with opioid use disorder or any other severe condition that can interfere in the participation or assessment of the study. Additionally, dropout rates are considered as treatment outcome although participants can dropout before starting CBT4CBT or TAU after arm allocation which would limit the power of the analysis. Finally, some patients will not be able to join the study if they live in a different area or attend to another treatment than day care. This is required for enabling the implementation of the full treatment and may be strength for homogeneity but it can also limit the generalization of results.

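### The primary-outcome definition of dropout requires an unanswered phone, so participants who leave but can be reached, or who ask to stop, do not count as dropouts

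*Protocol article*

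**What the plan says.** Aims of the study names retention as the first primary outcome: "two primary outcomes are considered: (1) treatment retention (vs. dropout", paired with relapse. Instruments then fixes the event as "treatment dropout (two consecutive failures to attend and not answering the phone". The next sentence gives the data source: "Treatment dropout will be determined throughout the attendance at the appointments with the clinician (TAU or TAU + CBT4CBT", with weekly appointments for 8 weeks and further checks at the follow-up points.

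Two provisions under Design and settings bear on this rule. One is the call: "after one unjustified absence rated by the psychologist, a phone call will be done". The other is withdrawal: "The intervention will be discontinued in case of request by the participant". The dropout definition does not mention withdrawal on request.

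Participants who leave between allocation and start appear in two places. The text after Figure 1 speaks of an imbalance in arm numbers "due to non-adherence to treatment protocol prior to starting CBT4CBT but after arm allocation, will also be centralized through Clinapsis". The Discussion, in its limitations, says "participants can dropout before starting CBT4CBT or TAU after arm allocation which would limit the power of the analysis".

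On the time of allocation, the text after Figure 1 says "After completing the inpatient care (at discharge of inpatient care), patients will be randomly assigned", and the abstract also places it after hospitalisation. Table 2 puts the Allocation mark in the enrolment column, although it has a separate column for the end of inpatient treatment.

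Data analysis assigns the primary objectives to Cox regression.

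**The concern.** A retention outcome should register everyone who ends treatment early. This definition adds a second condition, that the participant cannot be reached by phone, which measures contactability and not attendance. The protocol itself makes the call routine after one absence, so many leavers will be tested against that condition. Those who pick up and say they have left, and those who ask to stop, have clearly ended treatment, yet the rule does not name them as events.

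Lost events reduce power in a trial with only 37 per arm. The loss may also differ between arms. The trial is open-label, the psychologist judges whether an absence is justified, the same two researchers deliver the psychological strategies and carry out the assessments, and the CBT4CBT arm has a psychologist available whenever the program is used. If leavers in that arm are easier to reach, more of them would escape the count.

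The status of participants who never start matters because they are early leavers after randomisation. Cox regression needs a clear time origin and a clear set of people at risk.

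**Working it through.** **1. The rule applied to each type of leaver**

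| Participant | Two consecutive misses | Phone unanswered | Event under the stated rule |
|---|---|---|---|
| Stops attending, unreachable | yes | yes | yes |
| Stops attending, answers the call | yes | no | no |
| Asks to stop, reachable | yes, or visits cease by agreement | no | no |
| Leaves after allocation, before start | not stated | not stated | not stated |

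The sentence naming attendance as the source says where the data come from. It does not remove the phone condition.

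**2. The plan's own figure**

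Inputs from Sample size calculation: difference 2.1, SD 3.1, two-sided alpha 0.05, power 80%, drop-out 5%.

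n = 2 × (1.960 + 0.842)² × 3.1² / 2.1² = 34.2, rounded up to 35. Inflated: 35 / 0.95 = 36.8, rounded up to 37 per arm.

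This reproduces the stated 37 (a t-based version gives 36, then 38). The figure is not disputed. It is sized on positive urine specimens, not on dropout.

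**3. Equal under-count in both arms (assumed rates)**

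Recorded rate = true rate × share of leavers counted. Power is for two proportions with n = 37 per arm:

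Φ{ [ |p1 − p2| − 1.96 √(2p̄(1 − p̄)/n) ] / √[ (p1(1 − p1) + p2(1 − p2))/n ] }

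| True dropout | Share counted | Recorded | Power |
|---|---|---|---|
| 50% vs 30% | 100% | 50% vs 30% | 42% |
| 50% vs 30% | 75% | 37.5% vs 22.5% | 29% |
| 50% vs 30% | 50% | 25% vs 15% | 19% |
| 60% vs 30% | 100% | 60% vs 30% | 75% |
| 60% vs 30% | 75% | 45% vs 22.5% | 54% |
| 60% vs 30% | 50% | 30% vs 15% | 34% |

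The ratio of rates does not change (0.30/0.50 = 0.225/0.375 = 0.15/0.25 = 0.6). What is lost is events and power. The Cox model would give somewhat different figures; these show the order of the loss.

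**4. Unequal under-count (assumed rates)**

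Take true dropout of 40% in both arms, with 90% of TAU leavers and 60% of CBT4CBT leavers counted. Recorded: 0.40 × 0.90 = 36% and 0.40 × 0.60 = 24%, a 12-point difference where none exists. By the same formula, the chance of a significant result in favour of CBT4CBT is about 20%, against 2.5% with correct counting. Nothing in the documents supplies the 90% or the 60%.

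**5. Leavers before the start**

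The Design and settings text names non-adherence before CBT4CBT only. The Discussion names both arms and calls these people dropouts. Neither says whether they are events. To show what depends on the answer, assume 15 of 37 in an arm leave. Counting all gives 15/37 = 40.5%. If 2, 4 or 6 of them left before the start and were set aside, the rate would be 13/35 = 37.1%, 11/33 = 33.3% or 9/31 = 29.0%.

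**6. Allocation point**

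The abstract, Design and settings and the section on the web-based intervention all place assignment at or after discharge, a mean of 14 days from admission. Table 2 alone places it at enrolment. Its other rows keep their column positions, so a broken table is an unlikely cause.

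**The case against.** The best defence is that attendance is named as the source, and that scoring of requested withdrawals may sit in a full protocol or analysis plan that is not shown. That would explain an omission. It does not change a definition that is stated and that requires an unanswered phone.

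Several stronger readings are tempting, and the documents do not support them:

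- A reader might infer that every reachable leaver is permanently scored as retained. No sentence says so, and someone who answers one call, keeps missing visits and later stops answering can still meet the rule. Treating all who answer as uncounted gives an upper bound.
- A reader might infer that participants who leave before the start are replaced, re-randomised or excluded. The text says only that the imbalance is handled centrally in the platform, and the Discussion calls these people dropouts. The defect is an unclear status, not a stated exclusion.
- A reader might infer a false benefit for CBT4CBT. The call applies to both arms, and the Introduction says the face-to-face protocol is the same. Extra contact makes a difference possible, but does not show or size it.
- A reader might infer that Table 2 shifts the start of the dropout clock. No passage starts a clock from the table, so this is an inconsistency to correct.
- A reader might count a missed 6-month visit alone as a dropout that the rule overlooks. Months after an 8-week treatment, that is closer to loss to follow-up.

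**Conclusion.** The concern holds in a limited form and should be corrected. Followed literally, the stated definition leaves reachable leavers and requested withdrawals out of the event count of a primary outcome. Fewer events mean less power, and the omission could differ by arm.

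The actual size is unknown, because the documents give neither dropout rates by arm nor the share of leavers who answer the phone. The power losses and the 12-point example rest wholly on assumed rates; the fault in the definition does not depend on them. The unclear status of participants who never start and the Table 2 allocation mark are secondary points of consistency.

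**What to change.** These changes concern outcome scoring only. The phone call and the provision for stopping on request stay as they are.

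- During the 8 weeks, score dropout as two consecutive missed weekly appointments without return, or a request to stop, whichever comes first, regardless of phone contact. This keeps the two-miss tolerance, so one missed week-8 visit is not an event. State that the request concerns the outpatient treatment common to both arms; otherwise, stopping only the web program would be an event that TAU participants cannot have.
- Analyse all randomised participants in their allocated arm, with time from randomisation at discharge.
- Count those who never start as events dated at the first scheduled outpatient appointment. Survival time is then above zero, and Cox software does not discard them, as it may with events at time zero. Make the Design and settings text and the Discussion agree with this.
- Report attendance at the 1-, 3- and 6-month visits separately, as follow-up retention.
- Move the Allocation mark in Table 2 to agree with the text that randomises at discharge.

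The cost is a few sentences and one table cell, because attendance is already recorded. The downside is that the observed dropout rate will be higher.

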**Methods:**

All individuals coming for inpatient cocaine detoxification who meet the inclusion criteria will have the possibility to be part of the study. The participants of this open-label randomized controlled clinical trial (RCT) will be allocated to treatment as usual (TAU) or TAU+CBT4CBT after the hospitalization for cocaine detoxification. During the inpatient treatment they will all receive an individualized psychological intervention. There will be six time point assessments: at 48–72 h of starting inpatient treatment, at the end of inpatient treatment and before starting day care and outpatient treatment, at the end of the 8 weeks CTB4CBT / TAU arm treatment and at three follow-up time points (1-, 3-, and 6-months post-treatment).

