### Data analysis

Statistical programs SPSS 26.0 and Stata 15.1 for Windows will be used. The primary objectives of this study will be carried out through cox regression models. In addition, repeated measures ANOVA will also be performed to assess whether there is a time effect on the primary measures (treatment dropout and/or relapse) as well as secondary (craving, psychopathological state, recent cocaine use emotion regulation scores, trait impulsivity, other addictive behaviors) measures. In addition, these scores will be compared between the two treatment groups using a mixed model of repeated measures. All statistical tests will be two-tailed and will be considered significant if p <0.05. Also, for the characterization of the differences between men and women group comparisons will be conducted by means of chi-square tests (categorical variables) and *t*-tests (continuous variables). Finally, generalized linear models will be implemented to assess the psychopathological factors associated with treatment response. The need for the analyses to be adjusted for potential confounding variables that could introduce a bias in the results will be considered (e.g.,: age, psychopathology, among others). Especially if the study groups present an imbalance with confounding variables reported in previous literature.

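### The primary outcome treatment dropout is scored at the 1-, 3- and 6-month follow-up visits as well as during the 8-week treatment, so it mixes treatment retention with follow-up attendance

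*Protocol article*

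**What the plan says.** Aims of the study names as the first of two primary outcomes "treatment retention (vs. dropout"). Instruments defines the event as "treatment dropout (two consecutive failures to attend and not answering the phone") and bases it on attendance at the clinician appointments in either arm. The same sentence gives the timing of those appointments: "which will be carried out weekly during the 8-week period of treatment and at follow-up points".

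Assessment places the T2 visit "once the 8-w outpatient treatment is completed (TAU or TAU + CBT4CBT"), so the 8-week treatment ends at T2 in the control arm as well as in the experimental arm. The Methods part of the Abstract describes the later visits as "three follow-up time points (1-, 3-, and 6-months post-treatment").

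Data analysis adds: "The primary objectives of this study will be carried out through cox regression models". It states no end to the time window for dropout. The Discussion mentions dropout between allocation and the start of treatment, but not non-attendance after treatment has ended.

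**The concern.** Once the 8 weeks are over there is no study treatment left to drop out of, yet the definition can still generate a treatment-dropout event. Only patients still in treatment at week 8 can have such an event, so the arm that retains more patients has more patients exposed to it.

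The rule also changes meaning between the two periods. Two consecutive missed appointments are about two weeks of absence during treatment. In follow-up they are visits two or three months apart, and the event can be declared only at month 3 or month 6. As written, the rule could also join a missed week-8 appointment to a missed month-1 visit.

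At stake is one of two primary outcomes. Its result would depend partly on who returns for follow-up in an open-label trial, which is not the retention question in the aims.

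**Working it through.** **The plan's own figure.** Sample size calculation gives 37 per arm for a difference of 2.1 in positive urine specimens, SD 3.1, two-sided alpha 0.05, power 0.80 and 5% dropout. n = 2 × [3.1 × (1.960 + 0.842) / 2.1]² = 34.2, rounded up to 35; 35 / 0.95 = 36.8, rounded up to 37. The figure reproduces. It concerns urine specimens and does not depend on the dropout rule, so the document states no power for the retention comparison.

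**Who is misclassified.** A completer needs two consecutive misses among three follow-up visits (months 1 and 3, or months 3 and 6) plus an unanswered phone. If each visit is missed independently with assumed probability m, P(at least one miss) = 1 - (1 - m)³ and P(two in a row) = 2m²(1 - m) + m³. For m = 20% these are 49% and 7%; for m = 50%, 88% and 38%. The phone condition lowers the second figure further. Skipping one follow-up visit is therefore not enough.

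**Effect on the contrast.** Let p be the probability of dropout by week 8 and q the share of completers scored as dropouts in follow-up. Scored dropout is p + (1 - p)q. With equal q in both arms, the difference is (p_TAU - p_exp)(1 - q).

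The document gives neither p nor q. All rates below are assumptions: p = 50% (TAU) and 30% (TAU + CBT4CBT). The hazard ratio (HR) is the large-sample Cox estimate from a simulation with constant hazard over the 8 weeks, dropout recorded weekly and follow-up events at month 6. Dividing the follow-up events between months 3 and 6 changes it by less than 0.01.

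| q TAU / q experimental | Scored dropout, TAU / experimental | Difference | Cox HR |
|---|---|---|---|
| 0 / 0 | 50% / 30% | 20 points | 0.51 |
| 5% / 5% | 52.5% / 33.5% | 19 | 0.54 |
| 10% / 10% | 55% / 37% | 18 | 0.56 |
| 25% / 25% | 62.5% / 47.5% | 15 | 0.62 |
| 40% / 40% | 70% / 58% | 12 | 0.66 |
| 25% / 15% | 62.5% / 40.5% | 22 | 0.53 |
| 30% / 10% | 65% / 37% | 28 | 0.46 |
| 10% / 30% | 55% / 51% | 4 | 0.78 |

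The shortcut ln(S_exp)/ln(S_TAU), where S is the proportion not scored as dropout, gives ln 0.525 / ln 0.375 = 0.66 at q = 25%. It overstates the attenuation, because hazards are not proportional once follow-up events with equal risk by arm are added.

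**Share of events.** With 37 per arm, week-8 events number 18.5 + 11.1 = 29.6. At q = 25%, follow-up adds 0.25 × (18.5 + 25.9) = 11.1. So 11.1 / 40.7 = 27% of scored events would not be treatment dropout.

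**The case against.** Three arguments stand against the point.

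- **Long-term contact is a legitimate outcome.** The Introduction calls the disorder chronic, the aims look at treatment outcome at 1, 3 and 6 months, and the follow-up visits are appointments with the clinician. This supports reporting continued contact. It does not support counting its loss as treatment dropout when Assessment has the treatment already completed. If care is meant to continue after T2, the two sections still have to be reconciled.
- **Censoring rules usually belong in the analysis plan.** That is true of a missing rule. Here the Instruments section positively includes the follow-up points in the definition, so an analysis plan that followed it faithfully would carry the problem over.
- **The harm may be small.** The only attrition figure in the document is the 5% allowance in the sample size calculation. At q = 5% the assumed difference falls by one point. This stands: the size is unknown and could be minor.

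A reader might infer that the retention contrast must shrink toward no difference. The document does not support that. Shrinkage follows if completer loss is similar in the two arms, and nothing establishes that it will be. The trial is open-label, and the Introduction reports that earlier effects of the program lasted 6 months after treatment, so loss could well differ by arm. A reader might also infer that any completer who skips follow-up becomes a dropout, but the rule needs two consecutive misses and an unanswered call.

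**Conclusion.** The point holds as a defect of definition. As written, a patient who completes treatment can be scored as a treatment dropout, and no other section corrects this. The endpoint therefore does not measure the retention named in the aims.

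The numerical effect is conditional. With equal completer loss the risk difference is multiplied by (1 - q). On the assumed 50% against 30%, that means 19 to 12 points instead of 20, and a Cox HR of about 0.54 to 0.66 instead of 0.51, for q from 5% to 40%. With unequal loss the difference ranged from 4 to 28 points in the cases tried. None of these rates comes from the document. The change should be made because it is cheap and concerns a primary outcome, not because a bias of known size or direction has been shown.

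**What to change.** In Instruments, define the primary treatment-dropout event on the weekly appointments of weeks 1 to 8 only, keeping the existing rule of two consecutive misses plus an unanswered phone. In the Cox model for dropout, censor at week 8 the patients who are still attending, and say how a single missed appointment at week 8 is handled. Report attendance at 1, 3 and 6 months as a separate outcome, labelled study retention or continued contact.

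The cost is a sentence in the outcome definition and a stated censoring time. No new data are needed, and the 37 per arm is unaffected. The downside is fewer scored events in the primary dropout analysis; the events removed are those that arise after treatment has ended.
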